### Trial design

The trial will take place in a 52-week timeframe, including 26 weeks of treatment in both randomization groups. Metformin will be started at 500 mg b.i.d. (oral) and escalated to 1000 mg b.i.d. (4 tablets of 500 mg (=2000 mg)) 2 weeks thereafter. For participants aged 16–18 years, metformin dosage will be escalated to 500 mg b.i.d*. *maximum. Participants will undergo 4 main face-to-face visits after 0, 13, 26 and 52 weeks, as well as one short telephone visit after 2 weeks to evaluate the study medication dose (Table 1). Meanwhile, participants will undergo a lifestyle intervention that is considered care as usual in the participating centers. The study medication will start in the same seven days as the lifestyle intervention. The lifestyle intervention will exist of a combination of an exercise program and dietary interventions. The dietary intervention consists of five consultations with a dietitian in the first 26 weeks of treatment to stimulate both healthy food and appropriate caloric intake. The exercise program exists of minimally 60 min per week of unsupervised exercise by choice (i.e. walking, dancing, cycling or jogging). Also, participants gather in weekly lifestyle group sessions coached by an exercise professional with affinity in mental healthcare for low-intensity exercise including weekly weight measurements and assessment of physical activity using the Physical Activity Vital Sign questionnaire (PAVS) [40, 41]. Due to the COVID-19 pandemic, the weekly lifestyle sessions will be offered online. Participants may wish to discontinue lifestyle interventions at any moment and still continue with the current trial. Considering that some participants will discontinue lifestyle interventions in clinical practice, participants may carry on with the trial following the pragmatic design of this study to obtain results resembling clinical practice. Similarly, patients may continue with the trial after switching or stopping antipsychotic use. Patients should be on an antipsychotic at the start and may use any additional medicines except for medication(s) that inhibit(s) metabolism of metformin (e.g. bictegravir, cobicistat, daclatasvir, dolutegravir and vandetanib) or otherwise interact(s) with metformin (in particular those with possible detrimental effects on kidney functioning, e.g. NSAIDs, ACE-inhibitors, diuretics and intravascular iodine). Therefore, participants using the aforementioned medication will be excluded from this trial. Changes in medication use will be registered at each visit. Information regarding adherence to medication, dietary and exercise interventions is obtained by self-report during visits after 13 and 26 weeks. In addition, pill counts are used to assess medication use adherence. Participants are considered compliant in case of a pill count of > 80% [42, 43]. The adherence ratio will be calculated by the difference in the number of pills provided at visit 1 and the remaining pills at visit 3 and again between the number of pills provided at visit 3 and the remaining pills at visit 4 divided by the prescribed number of pills. This result will be multiplied by 100. To improve participant retention, participants will receive financial reimbursement for travel costs and 10 euros for each visit. Furthermore, the research team actively involved two experienced experts and patient association Anoiksis in the conceptualization and design of this study to ensure the design is patient-friendly, reflective of clinical practice and beneficial to patients.

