### Assessments

#### Visit 1

During visit 1, baseline demographic characteristics will be assessed. Medical history including medication-, alcohol, tobacco- and substance use, weight before the start of mental illness, weight before the initiation of antipsychotic use and the estimated amount of weight gained due to antipsychotic use is also collected. The M.I.N.I. plus section M is used to assess the criteria for schizophrenia [44, 45]. All elements of MetS (i.e. body weight and height, BMI, waist circumference, and systolic and diastolic blood pressure) are measured during a short physical examination. The 6 Minutes Timed Walking Test (6MTWT) and Simple Physical Activity questionnaire (SIMPAQ) are used to assess physical endurance and physical activity, respectively [46]. Blood glucose levels are measured using a capillary blood fingerdipstick and urine pregnancy tests will be conducted for women of childbearing age. Additionally, blood will be drawn to measure C-reactive protein (CRP), GFR, Triglycerides, Low-density lipoprotein (LDL) and High-density lipoprotein (HDL) levels, insulin, glucose and Hemoglobin A1c (HbA1c). At last, several questionnaires will be assessed during visit 1 (see ‘secondary outcomes’ below).

#### Visit 2

Visit 2 is a short visit by telephone at 2 weeks into the study to assess how the participant is proceeding with the study medication, i.e. whether they have been able to switch from the starting dose of 500 mg b.i.d. to 1000 mg b.i.d. and whether they are experiencing any side effects.

#### Visits 3 and 4

During visits 3 and 4, adherence to lifestyle interventions is assessed, as well as information regarding medication use, dose and side effects, adverse events reactions, alcohol-, tobacco- and substance use. Similarly to visit 1, physical endurance, physical activity and elements of MetS are measured during physical examination additional to the blood glucose level using a capillary blood fingerdipstick. Also, a urine pregnancy test and laboratory tests will be conducted. One EDTA tube (6 cc) or saliva is optionally drawn for DNA extraction. Furthermore, the same questionnaires as during visit 1 will be taken.

#### Visit 5

One year after completing study visit 1, body weight, waist circumference and blood.

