#### Data analysis

The primary analysis in this trial tests the effect of metformin use next to care as usual including lifestyle interventions on body weight with a primary comparison at 26 weeks after treatment onset. This will be analyzed using a general linear mixed model with treatment group, baseline weight, gender, age, timepoint (as categorical factor) and compliance with lifestyle therapy as fixed factors and patient as random factors. Measurements of visit 3 (week 13) and visit 4 (week 26) will be included in the primary analysis models. Missing baseline parameters will be imputed before the analyses, but mixed models can handle missing outcome variables at post-randomization weeks if these are missing at random (MAR). The pattern of missingness will be examined. As a sensitivity analysis, body weight at 26 weeks will also be analyzed using an ANCOVA with treatment group and gender as factors and baseline weight and age as covariates. The significance threshold is set at *p* < 0.05. Considering the study population, we expect a high number of dropouts [37]. Additionally, we expect participants within one stratification group may switch clozapine or other antipsychotic use. Taking into account the pragmatic design of this study, the Intention-To-Treat principle will be followed for the primary and secondary analyses. In secondary analysis, the effect of metformin on body weight after 26 weeks of treatment will be compared to body weight at 52 weeks after 26 weeks of non-treatment with metformin. In this way, we can examine whether the possible effect of metformin on AiWG continues after 26 weeks of non-treatment following discontinuation of metformin use after 26 weeks of treatment. In a sensitivity analysis, per-protocol analysis will be applied for all analyses. Non-adherent participants to study medication defined as less than 80% of pills being taken will be excluded (see ‘Trial design’) [42, 43].

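### The primary model adjusts for lifestyle compliance, which is measured after randomisation and can be changed by metformin, so it does not reliably estimate the intention-to-treat effect

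*Protocol article*

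**What the plan says.** Under Data analysis, the protocol article specifies a general linear mixed model for body weight at weeks 13 and 26, with the primary comparison at week 26. After treatment group, baseline weight, gender and age, it lists "timepoint (as categorical factor) and compliance with lifestyle therapy as fixed factors and patient as random factors". The same section states that "the Intention-To-Treat principle will be followed for the primary and secondary analyses". It also plans a sensitivity analysis of week-26 weight by "ANCOVA with treatment group and gender as factors and baseline weight and age as covariates", which has no compliance term.

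Trial design and Assessments show when compliance becomes known:

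- "The study medication will start in the same seven days as the lifestyle intervention", so compliance has no pre-treatment value.
- "Information regarding adherence to medication, dietary and exercise interventions is obtained by self-report during visits after 13 and 26 weeks".
- "During visits 3 and 4, adherence to lifestyle interventions is assessed". These are the visits whose weights enter the primary model.
- "Participants may wish to discontinue lifestyle interventions at any moment and still continue with the current trial". The stated reason is that results should resemble clinical practice.

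Data analysis then carries similar models to the secondary outcomes and the same model to the clozapine and high-risk-agent subgroups.

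**The concern.** Lifestyle compliance here is a consequence of what happens after randomisation. Two features of the design let metformin influence it. The group sessions involve "low-intensity exercise including weekly weight measurements", so participants see their weight change while deciding whether to continue. Metformin's side effects, which are asked about at the study visits, may also lead someone to give up exercise or dietitian appointments.

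If metformin changes compliance, adjusting for it does harm in two ways:

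- **Mediation.** Any part of the drug's effect that works through better or worse compliance is subtracted from the estimate.
- **Selection.** Compliance and weight probably share causes such as motivation and symptom level. Comparing arms within a compliance level then compares people who differ in those causes, and randomisation no longer protects the comparison.

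The trial's pragmatic question is what metformin does to weight whatever happens to lifestyle adherence, and the specified model does not target that. The ANCOVA without the term does, so the primary and sensitivity analyses address different quantities. At stake are the main estimate and its p-value. The bias can go either way and does not shrink with more participants.

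**Working it through.** **1. The plan's sample size.** From Sample size calculation: difference 2 kg, SD 4 kg, two-sided 0.05, 80% power, two-sample t-test. The normal approximation gives 63 per arm (126). The exact noncentral t calculation gives 79.5% power at 63 per arm and 80.1% at 64, hence 128. With 50% dropout, 128 / (1 − 0.5) = 256. Both figures reproduce. They rest on an unadjusted test, so the compliance term plays no part in them.

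**2. Mediation only.** Let T be the total effect of metformin on weight (kg, negative = loss), b the effect of complying on weight, and Δp the compliance proportion on metformin minus that on placebo. In a linear model:

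adjusted effect = T − b × Δp

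The documents give neither b nor Δp, so both are assumed. With T = −2, b = −3 and Δp = +0.10: −2 − (−3 × 0.10) = −1.7 kg, which is 15% too small. The range, with approximate power (normal approximation, 64 per arm, SD kept at 4, against 81% for the full 2 kg):

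| Extra loss in compliers | Δp = +0.10 | Δp = +0.20 | Δp = −0.10 | Δp = −0.20 |
|---|---|---|---|---|
| 2 kg | −1.8 (72%) | −1.6 (62%) | −2.2 | −2.4 |
| 3 kg | −1.7 (67%) | −1.4 (51%) | −2.3 | −2.6 |
| 4 kg | −1.6 (62%) | −1.2 (40%) | −2.4 | −2.8 |

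Power is not shown for the right-hand columns, because there the effect is overstated and higher power would mean nothing.

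**3. Shared unmeasured cause.** In a simulation, a participant complies when a·A + U + e > 0, with A the arm (1 = metformin) and U and e standard normal. Weight change includes −2U plus noise of variance 12, so the within-arm SD is √(4 + 12) = 4 kg when compliance itself does nothing. Setting a = ±0.6 gives compliance of about 50% on placebo and about 66% or 34% on metformin, a 16-point difference. With 1,000,000 participants per scenario:

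| True total effect | Effect of complying | Adjusted, compliance lower on metformin | Adjusted, compliance higher on metformin |
|---|---|---|---|
| 0 | 0 | −0.39 | +0.37 |
| 0 | −2 kg | −0.69 | +0.69 |
| −2 kg | 0 | −2.38 | −1.63 |
| −2 kg | −2 kg | −2.71 | −1.30 |

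In every row the analysis without compliance returned the true value to within 0.01 kg.

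**4. Type I error.** The setting is 64 per arm, no true effect, no effect of complying on weight, and 3,000 simulated trials per case. With the compliance term, rejection rates were 8.8% (compliance lower on metformin) and 8.0% (higher). Without it they were 5.4% and 4.7%.

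**5. No effect of metformin on compliance.** With a = 0, type I error was 5.4% with the term and 5.8% without. A separate large simulation with a 3 kg compliance effect and 50% compliance in both arms gave −1.702 kg adjusted against −1.704 kg unadjusted. There is no bias in this case.

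Steps 3 to 5 use a single time point and leave out baseline weight, age and gender. They show the mechanism and its scale and do not replicate the two-visit mixed model.

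**The case against.** The strongest reply is that the harm is conditional. Nothing in the document says metformin changes lifestyle compliance. The trial is double-blind with matched placebo and both arms receive the same programme, so only drug-driven routes remain. If these are negligible, step 5 applies. That is correct, and the bias should be described as possible, of unknown size and sign. But the condition cannot be known in advance, and a randomised primary analysis should not depend on it. Blinding does not close the routes, which run through weight change and side effects that participants experience.

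Second, the assumed compliance effects are large beside a 2 kg design difference. With 1 kg and 10 points, the mediation bias is 1 × 0.10 = 0.1 kg, or 5%. This is fair, and it sets the lower end of the plausible range.

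Third, the weight-loss route needs a real drug effect, so it cannot create a false positive on its own. This also stands: the 8 to 9% needs another route, such as side effects, together with a shared cause.

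Fourth, the ANCOVA without compliance would expose a discrepancy. It helps, but it is a sensitivity analysis of week-26 weights only, with up to 50% dropout expected, and it does not replace the primary result.

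A visit with weight recorded but compliance missing would also be lost under default model fitting. That depends on coding and missing-data handling that the article does not describe, so it is a minor point here.

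**Conclusion.** The concern holds. The article itself fixes a post-randomisation covariate in the primary model, beside a commitment to intention to treat and a pragmatic rationale that both call for leaving it out. Under the assumed ranges (compliers lose 2 to 4 kg more, compliance differs by 10 to 20 points), a true 2 kg effect is estimated as 1.2 to 2.8 kg, an error of up to 40% in either direction. Where compliance is higher on metformin, power falls from about 81% to between 72% and 40%. With a shared cause and a 16-point difference, a true null is shifted by about 0.4 kg, or 0.7 kg if complying also lowers weight by 2 kg. These sizes are illustrative, and the bias is zero if metformin does not affect compliance. The term is not needed for precision either, since the sample size was set without any covariate adjustment.

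**What to change.** Delete lifestyle compliance from the primary mixed model, leaving treatment group, baseline weight, gender, age and timepoint as fixed effects and patient as random. Any covariate added should be fixed at or before randomisation. Make the same deletion in the secondary-outcome and subgroup models derived from it. Report lifestyle compliance by arm at weeks 13 and 26 descriptively. If a compliance-adjusted model is still wanted, label it exploratory and state what quantity it estimates and on what assumptions.

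The cost is one term removed from the model wording before unblinding. No new data are needed, and the targets of 128 completers and about 256 recruited stay as they are.

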pressure are measured during physical examination and the 6MTWT is performed to assess physical endurance [46]. Furthermore, information regarding medication use and the (off-label) prescription of metformin between 26 weeks and 52 weeks by other physicians is assessed.

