### Secondary outcomes

Differences between the two arms from treatment inception until 26 weeks of treatment in:
Any element of MetS (i.e., waist circumference (cm), BMI (kg/m^2^), triglycerides (mmol/L), LDL (mmol/L) and HDL (mmol/L) levels in blood, blood pressure (mmHg) and HbA1c (mmol/mol)) [3].Response, defined as ≥5% body weight loss at 26 weeks relative to treatment inception.Quality of life measured using the WHOQOL-BREF, a shorter version of the World Health Organization Quality of Life instrument [47].Quality of life measured using the complementary 3-level version of the EuroQol 5D (EQ-5D-3L) [48].General psychological and physical health using the brief Clinical Global Impression-Severity and -Improvent scale (CGI-S and CGI-I) [49].General psychological and physical health using the Brief Psychiatric Rating Scale (BPRS) [50].Potential fluctuations in depressive, positive and negative symptoms using the The Community Assessment of Psychic Experiences (CAPE) scale [51, 52].Cost-effectiveness using the iMTA Productivity Cost Questionnaire (iPCQ) and the iMTA Medical Consumption Questionnaire (iMCQ) [53].

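### The 52-week analysis names no contrast with placebo at week 52 and makes no stated use of recorded off-label metformin, so its persistence conclusion is not supported as written

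*Protocol article*

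**What the plan says.** The Data analysis section plans a secondary analysis whose subject is the metformin effect: "body weight after 26 weeks of treatment will be compared to body weight at 52 weeks after 26 weeks of non-treatment with metformin". It then states the purpose: "we can examine whether the possible effect of metformin on AiWG continues after 26 weeks of non-treatment following discontinuation of metformin use".

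Other parts of the protocol article bear on this:

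- **Assessments, Visit 5:** body weight is measured one year after visit 1, and "information regarding medication use and the (off-label) prescription of metformin between 26 weeks and 52 weeks by other physicians is assessed".
- **Trial design:** both arms receive 26 weeks of study treatment within a 52-week timeframe. The dietary part of the lifestyle intervention is "five consultations with a dietitian in the first 26 weeks of treatment".
- **Data analysis, primary model:** "Measurements of visit 3 (week 13) and visit 4 (week 26) will be included in the primary analysis models".
- **Secondary outcomes:** the list is introduced as "Differences between the two arms from treatment inception until 26 weeks of treatment in", so weight at week 52 is not on it.
- **Data analysis, analysis principle:** "the Intention-To-Treat principle will be followed for the primary and secondary analyses".

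**The concern.** Two things do not fit the conclusion that the analysis is meant to support.

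First, the sentence sets an effect (at week 26) against a body weight (at week 52). These are different quantities. No arm or between-arm contrast is given for week 52. Followed literally, the comparison becomes week 26 against week 52 among those who took metformin. Anything else that changes after week 26 then enters the result. The dietitian consultations are one documented example.

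Second, the analysis treats weeks 26 to 52 as free of metformin, while visit 5 provides for recording metformin prescribed by others in that same period. Nothing in the article connects that record to the analysis.

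The trial is meant to inform guidelines. It could report that a benefit persists off drug when some participants are still taking it. It could report that a benefit is lost when both arms regained weight. It could also understate real persistence if former placebo participants start metformin.

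**Working it through.** **Inputs from the article (Sample size calculation):** effect 2 kg, SD 4, two-sided 0.05, 80% power, 128 completers, at most 50% dropout.

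**Inputs not in the article, assumed here:** off-label shares at week 52 of 0 to 50% in the former metformin arm (pM) and the former placebo arm (pP); weight drift common to both arms between weeks 26 and 52 (g) of −2 to +2 kg; anyone on metformin at week 52 has the full 2 kg effect.

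**Step 1. Reproduce the plan's figure.** With effect size 2/4 = 0.5, the exact t-test needs 63.77, so 64 per arm or 128 in total, with power 0.801. Then 128/(1 − 0.5) = 256. Both figures reproduce. The article gives no figure for the 52-week comparison, so the rest is illustration.

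**Step 2. Within-arm reading, no off-label use.** Change from week 26 to week 52 in the former metformin arm = g + effect lost.

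- Full persistence (0 kg lost): −2 to +2 kg.
- No persistence (2 kg lost): 0 to +4 kg.

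The ranges overlap from 0 to +2 kg. A rise of 1 kg, for example, fits full persistence with g = +1 and also no persistence with g = −1. This comparison cannot separate persistence from drift.

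**Step 3. Within-arm reading, with off-label use.** With no persistence and g = 0, regain = 2 × (1 − pM): 2.0 kg at 0%, 1.6 kg at 20%, 1.0 kg at 50%. Continued use looks like partial persistence.

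**Step 4. Between-arm reading at week 52.** Count the difference as positive when the former metformin arm is lighter. Common drift g cancels. Off-label use does not.

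- No persistence: 2 × pM − 2 × pP = 2 × (pM − pP).
- Full persistence: 2 − 2 × pP.

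| pM | pP | No persistence (kg) | Full persistence (kg) |
|---|---|---|---|
| 0% | 0% | 0 | 2.0 |
| 20% | 0% | +0.4 | 2.0 |
| 20% | 20% | 0 | 1.6 |
| 0% | 20% | −0.4 | 1.6 |
| 50% | 0% | +1.0 | 2.0 |
| 0% | 50% | −1.0 | 1.0 |

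A week-52 difference of 1.0 kg can therefore arise with no persistence (pM = 50%, pP = 0) or with full persistence (pP = 50%). For scale, the standard error of a simple between-arm difference with 64 per arm and SD 4 is 4 × √(2/64) = 0.71 kg, if everyone seen at week 26 is also weighed at week 52.

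**Step 5. Does other text settle it?** The primary model stops at week 26, and so do the listed secondary outcomes. The per-protocol rule works on study-pill counts, which end at visit 4 (week 26), so it cannot address metformin taken afterwards. Intention-to-treat points to comparison by allocated arm, which is the reading in step 4, with off-label users included.

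**The case against.** The strongest defence is that the sentence speaks of an effect of metformin, which in a placebo-controlled trial is a between-arm quantity. The preceding text applies intention-to-treat to the secondary analyses, and both arms are followed and weighed at week 52. Off-label use is foreseen and recorded. Protocols commonly state a planned regimen and record departures from it, and detailed handling of such events may sit in an analysis plan that is not shown.

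Much of this stands, and it rules out several stronger readings that a reader might infer:

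- *That the article fixes a before-after comparison, or that persistence can never be inferred from this trial.* The wording permits a randomised reading and the data for it are collected. This is a fault of wording and estimand, not of design.
- *That off-label use would create false persistence of some definite size.* The article gives no uptake rate. If uptake is equal in the two arms, the between-arm distortion under no persistence is zero, and if it is higher in the former placebo arm the sign reverses.
- *That all lifestyle support stops at week 26.* Only the dietitian consultations are specified for the first 26 weeks. The article does not say when the group sessions or exercise end.

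The defence does not remove the point. The question is what the article concludes from the comparison it states, and not only how much detail it gives. Even on the favourable reading, an intention-to-treat contrast at week 52 estimates the effect of original allocation, whatever was taken later. It does not show what happens after 26 weeks without metformin.

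**Conclusion.** The point holds in this form: the conclusion that the effect continues after stopping is not supported by the analysis as written. The week-52 contrast with placebo is not named, and the off-label record has no stated use in the analysis. Under the planned 2 kg effect, full effect in current users and off-label shares of 0 to 50%, the week-52 between-arm difference would run from −1.0 to +1.0 kg with no true persistence, and from 2.0 down to 1.0 kg with full persistence. The shares are assumptions, so the actual size and direction are unknown. The issue touches one secondary analysis. It leaves the primary outcome, the sample size and the data collection unaffected, and it should be corrected before the 52-week data are analysed.

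**What to change.** 1. Define the secondary analysis as the randomised metformin-minus-placebo difference in body weight at week 52, together with its change from week 26.
2. Estimate both from a secondary fit of the mixed model that adds week 52 and a treatment × timepoint term. The listed model has neither. The primary analysis can keep weeks 13 and 26.
3. Describe the result as a treatment-policy effect after the end of study treatment, and drop the description of weeks 26 to 52 as a period without metformin.
4. Report off-label metformin use in weeks 26 to 52 by arm.
5. For the off-drug question, add a sensitivity analysis, for example setting weights after the start of off-label metformin to missing and imputing them. State the missing-at-random assumption openly: it is doubtful if those who regain weight are the ones prescribed metformin, so this should support the main contrast and not replace it.

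The cost is wording plus one extra sensitivity analysis with somewhat wider intervals. Visit 5 already collects both weight and off-label prescription, so no new data are needed.
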